## **5 STATISTICS AND METHODOLOGY**

### **5.1. Statistical analysis plan and sample size calculation**

A statistician was involved in the study design and estimate of the sample size.

Null hypothesis  $H_0$ : EEN has no effect on postoperative complications (CCI) in the population (and therefore the observed effect is entirely due to chance):  $p_2 = p_1$

Scientific hypothesis  $H_1$ : EEN has an effect on postoperative morbidity (CCI) in the population (and therefore the observed effect is not entirely due to chance):  $p_2 > p_1$

According to a previous randomized trial including a series of PD and assessing a realimentation process (enteral vs. parenteral), the mean CCI was impacted of about 30% (32.8 vs. 24.2). Another study reported a mean CCI of 38 after PD.

Based on the above results, we hypothesize that EEN will reduce by 30% a mean CCI of 35 (+/- 20) of the oral nutrition group. We will therefore expect a mean CCI for the treatment group (EEN) of 24.5 (SD 20). In this superiority study, for a power of 80% and a significance level of p-value  $\leq 0.05$  (two-sided alpha), we will therefore need 57 patients per group according to the sample size calculation. Nevertheless, we will increase the sample size to a total of 144 patients to take into account 20% of drop-outs (e.g., due to non realization of pancreatoduodenectomy or consent withdraw) at 90 days (primary endpoint evaluation). We will therefore need to enroll 72 patients per group in the trial.

The study will be closed once the required 144 patients will be included. No interim analysis will be performed.

Normality of distribution will be determined by the Kolmogorov-Smirnov test and quantile-quantile plots of dependent variables for all continuous variables.

We will use a Student *t*-test to evaluate if the primary outcome (CCI) can significantly be reduced by EEN compared to the control group (comparison of mean CCI hypothesizing a normal distribution). For the analysis of all secondary endpoints, we will also use *t*-tests or chi-squared tests based on the variable types. Regarding the questionnaires filled 4 times during the study, tests specific to repetitive ordinal measures will be used.

The analysis will be based on the intention-to-treat method and not per protocol. We will perform an intention-to-treat analysis so that all patients being intended to treat will be analyzed in the statistics independently. All patients will therefore be analyzed according to the group in which they were initially randomized.

Blocked randomization will be done using a computerized algorithm via REDCap by a research coordinator (different from the person who included the patient) the day before surgery. The proportion of "study" (EEN) and "control" (oral nutrition) subjects will be 1:1 (mix of variable block sizes of 4, 6, and 8 patients, randomly selected). Before surgery, only the responsible surgeon will know the allocation group. Postoperatively, the inclusion in the different groups will be known by the caregiver team and the patient, as it is not possible to blind the intervention (nasojejunal tube).

The investigators, the outcome adjudicators, and the data analysts will be blinded (allocation concealment).

The statistical package used for analysis will be SPSS version 26 (IBM Corp., Armonk, NY, USA).

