| Number of Participants with Rationale | 
According to a recent randomized trial including a series of PD and assessing a realimentation process (enteral vs. parenteral), the mean CCI was impacted by about 30% (32.8 vs. 24.2). Another study reported a mean CCI of 38 after PD. We hypothesized that ENN would reduce a mean CCI of 35 (± 20) by 30%.
 
Assuming a CCI reduction of 10.5 points (30% of 35), a standard deviation of ± 20, a 80% power, an alpha of 5% and a dropout rate of 20%, the total required number of patients is 144 (72 study patients = EEN group and 72 control patients = oral nutrition group).
                                                                                                                                                                                                                                                                                                                                                                                                                                                                                                                                                                                                                                                                                                                                                                                                                |

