## 2 BACKGROUND AND RATIONALE

Pancreatic cancer (PAC) is one of the deadliest cancers in humans (more than 47'000 estimated deaths in 2020 in the United States). It is predicted to become the second most common cause of cancer deaths in the United States by 2030^2. The mean costs in 2015 were estimated to be \$79'800 per patient with PAC and \$164'100 for each resection. The observed overall 3-year survival after diagnosis is 6%. The majority of PAC are adenocarcinomas and approximately 60-70% of them are localized in the head of the pancreas. To date, surgery remains the only potentially curative strategy. However, resection of the pancreatic head remains a difficult surgical procedure embedded with high morbidity (40-60%). Recently, the concept of Enhanced Recovery After Surgery (ERAS) has contributed to reduce overall morbidity, length of hospital stay and costs by implementing multimodal measures influencing the pre-, intra- and postoperative periods.

Patients suffering from pancreatic tumors as well as patients with chronic pancreatitis often present with cachexia or at least with a certain level of malnutrition. This situation is difficult to correct preoperatively due to the pressure to operate these patients rapidly. Nutritional therapy should therefore be started early during the postoperative course to prevent further malnutrition, as the latter is an important risk factor to develop complications. This is even more relevant for patients with poor preoperative nutritional status. In addition, surgery disrupts the digestive tract, leading to postoperative indigestion and malabsorption. Postoperative nutritional supports, including early enteral nutrition (EEN) and total parenteral nutrition (TPN), have been shown to be effective in improving clinical outcomes after major abdominal surgery.

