# **7 FURTHER ASPECTS**

## **7.1 Overall ethical considerations**

The study design (randomized controlled trial) will permit to have a good internal validity of the study. Moreover, the CCI used as main outcome is a validated index of general postoperative morbidity and it enables to encompass all complications that a patient may present. The inclusion of several centers internationally will increase the generalizability of the results (external validity). The complication rate after PD remains high (around 60%) and malnutrition has been established as a risk factor of postoperative complication. An intervention that could improve the nutritional status of the patients might lead to a decrease of morbidity after PD.

If the results are favorable, this study will permit to establish an EEN protocol to improve patient outcomes after PD. Patients undergoing PD could rapidly benefit of this management, and EEN could become the new standard of care for the perioperative nutrition management after PD. The results of this study could be implemented and translated into daily clinical practice promptly.

The need for research in this field is clearly present, as the issue of postoperative nutrition after PD is not resolved and does not reach an overall consensus among international pancreatic surgeons. The numerous presentations, debates in congresses, and our recently published survey on that subject attest and highlight the absence of universal consensus and lack of solid data.

The results of this study would go beyond the only scientific interest, as they will directly impact patients undergoing pancreas surgery. As pancreas cancer incidence is projected to grow in the upcoming years, pancreas surgery number will correlatively increase. Ultimately, in the current era of growing health expenditures and need for cost containment, if EEN allows decreasing complications and length of stay, it could also decrease the overall costs for each patient hospitalization for PD, which could have important positive repercussions on the health care system.

Particular attention will be paid to the process of randomization in order to ensure a sound methodology.

An overall fair balance for the study participant will be maintained.

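### The planning SD of 20 has no stated source and does not fit a mean CCI of 35 at the protocol's own complication rate of about 60%; if that rate applies, power is at most about 62%, not 80%

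*Protocol*

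**What the plan says.** Section 5.1 sets the planning values: "we hypothesize that EEN will reduce by 30% a mean CCI of 35 (+/- 20) of the oral nutrition group", and for the intervention arm "We will therefore expect a mean CCI for the treatment group (EEN) of 24.5 (SD 20"). The target difference is therefore 10.5 points with the same SD in both arms. The resulting size is given as ("two-sided alpha), we will therefore need 57 patients per group according to the sample size calculation"), raised to 72 per group and 144 in total for 20% drop-out. The synopsis repeats the inputs: "Assuming a CCI reduction of 10.5 points (30% of 35), a standard deviation of ± 20, a 80% power, an alpha of 5"%. The primary test is a Student t-test on mean CCI, and no interim analysis is planned.

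Section 5.1 supports the mean with two cited studies of pancreatoduodenectomy (PD): one with means of 32.8 and 24.2, the other with a mean of 38. It gives no source or derivation specific to the SD.

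Elsewhere the protocol gives complication rates. Section 7.1 says "The complication rate after PD remains high (around 60"%), and section 2 says that resection of the pancreatic head "remains a difficult surgical procedure embedded with high morbidity (40-60"%). Section 7.1 describes the CCI by saying that "it enables to encompass all complications that a patient may present".

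**The concern.** The CCI summarises all complications, so a patient who has none should score 0. If about 40% of patients score 0 and the overall mean is still 35, the others must average 35/0.60 = 58.3. A distribution split between 0 and values around 58 is necessarily wide, and 20 is too small an SD for it.

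The sample size depends on the square of the SD. If the true SD is nearer 25-29 than 20, 57 patients per group do not give 80% power for 10.5 points, and a non-significant result would carry much less information than the protocol implies. This is not something left to a later analysis plan: the protocol fixes the inputs and the power claim in section 5.1 and in the synopsis.

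**Working it through.** **Inputs from the protocol.** Control mean 35, EEN mean 24.5, SD 20 in both arms, two-sided alpha 0.05, power 80%, 57 evaluable and 72 enrolled per group (section 5.1); complication rate around 60% (section 7.1) or 40-60% (section 2 and the synopsis background).

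**Assumptions added here.** A patient without a complication has CCI 0 (inferred from the index summarising all complications, not stated outright). The quoted rate is the share p of patients with CCI above 0. The SD among complicated patients, w, is not in the protocol; 0 is the most favourable value and 15 is used as an illustration.

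**Step 1: the plan's own figure.** n per group = 2(1.96 + 0.8416)² × 20² / 10.5² = 56.95, so 57. Then 57/0.80 = 71.25, so 72 per group and 144 in total. The stated size is correct on its stated inputs. Exact t-test power at 57 per group is 79.4% (80.0% by the normal approximation).

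**Step 2: the smallest SD compatible with mean m and rate p.**
Variance = m²(1/p − 1) + p·w². With w = 0 this is a minimum, so SD ≥ m√((1 − p)/p).

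For the control mean of 35:
- p = 0.60: 35 × √(0.40/0.60) = 28.6
- p = 0.50: 35.0
- p = 0.40: 42.9

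No rate in the protocol's 40-60% range allows an SD of 20. Solving for SD = 20 gives p = 35²/(35² + 20²) = 1225/1625 = 75.4% with no spread among complicated patients. With w = 15 the required rate is about 86%.

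For the EEN mean of 24.5, the minimum SD is 20.0 at p = 0.60. If EEN acts by cutting the rate by 30%, to 0.7 × 60% = 42%, the minimum is 28.8.

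**Step 3: power for 10.5 points** (t-test, two-sided 5%, pooled SD = √((SD₁² + SD₂²)/2)).

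| Scenario | SD control / EEN | Pooled SD | Power, 57 per group | Power, 72 per group |
|---|---|---|---|---|
| As planned | 20 / 20 | 20 | 79% | 88% |
| 60% in both arms, w = 0 | 28.6 / 20.0 | 24.7 | 62% | 72% |
| 60% in both arms, w = 15 | 30.8 / 23.1 | 27.3 | 53% | 63% |
| 60% control, 42% EEN, w = 0 | 28.6 / 28.8 | 28.7 | 49% | 59% |

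The rows with w = 0 are ceilings for their scenario; any spread among complicated patients lowers the power.

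**Step 4: detectable difference at 80% power, 57 per group.** (1.96 + 0.8416) × pooled SD × √(2/57) gives 12.9 for 24.7, 14.3 for 27.3 and 15.1 for 28.7: about 13-15 points, or 37-43% of 35, against the planned 10.5 (30%).

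**Step 5: what rate would restore 80%?** With the same rate in both arms, the pooled SD falls to 20 at about 70% if w = 0 and at about 81% if w = 15. If EEN also lowers the rate, more is needed: 80% control and 56% EEN gives 80% power with w = 0 but 67% with w = 15.

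**The case against.** The strongest reply is that section 5.1 contains no arithmetic error and does not use the 60%. That figure is a round number for PD in general, taken from the ethics section, and the 40-60% is background. The trial enrols only patients with NRS ≥3, and section 2 says such patients are considered to have more, and more severe, complications. Neither section says which grades or what follow-up the rates cover, whereas the CCI here counts everything within 90 days. The share of control patients with CCI above 0 could therefore exceed 60%, and from about 75% an SD of 20 becomes possible.

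Most of this stands, and it limits what can be claimed. A reader might infer that the SD of 20 is simply impossible, or that the trial's power is in fact 49-62%. The documents support neither. Mean, SD and rate conflict, but the conflict alone does not show which of the three is wrong, and the protocol gives no rate for this control arm.

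It does not remove the conflict. The means behind the 35 are also cited as results after PD, so mean and rate rest on the same general basis, and section 7.1 uses the 60% to justify this trial. Of the three figures, only the SD has no source of its own. A moderately higher rate is not enough either: at 75% in both arms with w = 15, power at 57 per group is 72%.

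It can also be said that 72 per group are enrolled. With no drop-out at all, the 60% scenarios in the table still reach only 59-72%.

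**Conclusion.** The point holds in conditional form. Taking CCI as 0 without a complication, a mean of 35, an SD of 20 and a complication rate of about 60% cannot all describe the same control arm: the SD would be at least 28.6. If the 60% applies, power for 10.5 points with 57 evaluable per group is at most about 62% with both arms at 60%, about 53% with an assumed spread of 15 among complicated patients, and at most about 49% if EEN lowers the rate to 42%. The 62% ceiling assumes that EEN does not have a higher complication rate than control with milder events.

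The stated 80% is plausible only at a control rate well above the protocol's figures, roughly 70-80% or more depending on spread and on how EEN acts. That may be true of patients with NRS ≥3, but the protocol does not say so. The test and the analysis population are unaffected. What needs correcting is a power claim resting on an unsourced SD. This is a should-fix.

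**What to change.** In section 5.1 and in the synopsis entry on the number of participants:

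- State the expected control-arm complication rate for patients with NRS ≥3 and make it consistent with the mean and the SD, using SD ≥ m√((1 − p)/p) as a minimum check.
- Give the source of the SD. If CCI data have accrued, check it against the blinded pooled SD, which needs no comparison between arms.
- Restate the power for 57 evaluable patients per group, or the difference detectable with 80% power (about 13-15 points if the 60% rate holds). The replacement figure should follow from the sourced inputs and should not be fixed in advance.

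The cost is a few sentences in two places and, where data allow, one blinded SD. Enrolment need not change to correct the claim. The downside is that the stated power will probably look less favourable.

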- Various malabsorption due to PD surgery: measurements will be made twice, once before surgery and once between the 4th and 6th postoperative week during the follow-up visit. As PD might induce duodenal and pancreatic insufficiencies postoperatively due to the resection of the duodenum and the pancreatic head, it is presently unknown if EEN might have an effect on these insufficiencies by improving the overall nutritional state and the mucosal trophicity of the small bowels.
  - Duodenal insufficiency: folate, magnesium, calcium, iron, ferritin, transferrin saturation
  - Exocrine pancreatic insufficiency: malabsorption of fat soluble vitamins: vitamin D (with calcium/phosphate balance and parathormone) and vitamin E
  - Endocrine pancreatic insufficiency: due to risk of developing a secondary diabetes, HbA1c (glycated hemoglobin) will be measured.
- Body measure using bioelectrical impedance analysis (BIA) and muscle strength using handgrip will be measured preoperatively, on discharge day, and on the first follow-up visit.
- Resting energy expenditure will be measured on POD 5 using indirect calorimetry.

Each of these endpoints will be measured in the study (EEN) and control (oral nutrition) groups.

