- On POD 4: normal diet (full portion)

From POD 1, patients of both groups will receive two oral nutritional supplements (Resource® Ultra XS 125 ml, 280 kcal, 18 grams of proteins or analogous products) until discharge. In terms of intravenous infusions, a parenteral crystalloid solution will be used (Ringer-Lactate): 1000 ml during operative day and on POD 1, 500 ml during POD 2 and 3, then 250 ml, if necessary, NUTRIWHI Trial

until POD 8 (minimum for maintenance of the central venous line). Anti-nausea agents (ondansetron 4 mg 3x/j and mephameson 4 mg 1x/j) as well as laxatives (magnesium hydroxyde 4.5 g 2x/j) will be used daily for 3 days, then on demand. Prokinetic agent (metoclopramide 10 mg 3x/j) will be used on demand. An anti-acid (esomeprazole 40 mg 1x/j) will be introduced for the duration of the hospitalization. Digestive enzymes will be prescribed from the first postoperative day (Creon 40'000 UI 3x/j).

In terms of mobilization, patients will be stimulated by nurses/physiotherapists according to the following plan:

- Operative day: just get up from bed
- On POD 1: walk once during the day, spend  $\geq 6$ h out of bed (3 x 2h)
- On POD 2 to discharge: walk twice during the day, spend  $\geq 8$ h out of bed (4 x 2h)

In our current practice, no suction gastric tube is left in place after the operation.

A standard nutrition protocol for the EEN intervention group will be prescribed as established in accordance with the nutritionists (see "3.4 Study intervention" for details). For patients randomized into the oral nutrition group they will receive the current postoperative management and receive from POD 1 an oral nutrition that will be gradually increased if tolerated until a normal diet (see above).

Several blood tests will be performed during the postoperative period. A timeline summary table of all study visits, relevant procedures, and samplings is shown in Appendix 1 (schedule of assessments).

Demographic disparities or difference in patient characteristics could be a source of bias. To reduce this risk, we decided to undertake a randomization of the participants. Moreover, heterogeneity in general management between centers might be a source of bias. Randomization will be stratified by center to decrease the risk of center bias.

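### Randomisation is stratified by centre, but the stated tests leave centre out and name no baseline covariate: a small, conservative loss of precision for CCI and a possibly larger one for secondary measures with a preoperative value

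*Protocol*

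**What the plan says.** - **Design (Protocol 4.3).** "Randomization will be stratified by center to decrease the risk of center bias". The reason given is that general management may vary between centres. The synopsis lists three centres.
- **Primary analysis (Protocol 5.1).** A Student t-test is to be used "to evaluate if the primary outcome (CCI) can significantly be reduced by EEN compared to the control group", as a comparison of mean CCI. No centre term is mentioned, and the synopsis says the same.
- **Secondary analyses (Protocol 5.1).** "For the analysis of all secondary endpoints, we will also use" t-tests or chi-squared tests, chosen by variable type. Section 5.1 makes one exception: the questionnaire completed four times (QLQ-C30) gets tests for repeated ordinal measures, which are not named. The synopsis omits this exception.
- **Baselines collected (Protocol 3.2).** Lean body mass and handgrip "will be measured preoperatively, on discharge day, and on the first follow-up visit". Metabolic laboratory values, malabsorption laboratory values and QLQ-C30 also have a preoperative measurement.
- **Adjustment (Protocol 5.2).** The missing-data section foresees imputing adjustment variables. No analysis in section 5.1 names or uses any.

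**The concern.** Blocking within centre keeps the arms balanced at each centre, so differences between centres largely drop out of the treatment contrast. A two-sample t-test does not take this into account. It leaves the between-centre variance in its error term, so its standard error is larger than the true sampling variability of the contrast. The p-value is then too large on average, the confidence interval too wide, and some power is lost.

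A separate issue concerns secondary measures with a preoperative value. A comparison of follow-up values alone discards information that the trial already pays to collect.

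These are methods the protocol states, not details it leaves open. They do not match its own design or its own reference to adjustment variables.

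**Working it through.** **Inputs from the protocol.** The synopsis gives the effect, SD and power: "Assuming a CCI reduction of 10.5 points (30% of 35), a standard deviation of ± 20, a 80% power". It also gives "an alpha of 5% and a dropout rate of 20" per cent. Section 5.1 gives the sidedness and group size: "two-sided alpha), we will therefore need 57 patients per group according to the sample size calculation". Allocation is 1:1.

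**Inputs assumed.** The share s of CCI variance lying between centres is taken as 2% to 10%, with 20% as an extreme. The correlation r between preoperative and follow-up values is taken as 0.4 to 0.6. The protocol gives neither.

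**Step 1: reproduce the plan's figure.** n per group = 2 × (1.960 + 0.842)² × 20² / 10.5² = 56.95, rounded up to 57. With 20% dropout, 57 / 0.8 = 71.25, rounded up to 72, or 144 in total. This agrees with section 5.1: "we will increase the sample size to a total of 144 patients to take into account 20% of drop-outs". An exact t-based calculation gives 58 per group, one more. The sample size is not at fault.

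**Step 2: effect of leaving centre out of the CCI test.** With allocation balanced within centre:

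- true SE = 20 × √(1 − s) × √(2/57)
- SE used by the plain t-test = 20 × √(2/57)
- ratio of used to true SE = 1/√(1 − s)
- true two-sided type I error = 2 × [1 − Φ(1.96/√(1 − s))]

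The power columns use the t distribution with 57 per arm and a difference of 10.5. Both tests are evaluated under the same stratified allocation.

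| s | SE overstated by | True type I error | 95% CI half-width, used vs correct | Power, unadjusted | Power, centre in model |
|---|---|---|---|---|---|
| 2% | 1% | 4.8% | 7.34 vs 7.27 | 79.6% | 80.1% |
| 5% | 3% | 4.4% | 7.34 vs 7.16 | 79.9% | 81.3% |
| 10% | 5% | 3.9% | 7.34 vs 6.97 | 80.6% | 83.4% |
| 20% | 12% | 2.8% | 7.34 vs 6.57 | 81.9% | 87.4% |

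The half-widths use the normal quantile. The power difference is 0.5 points at 2% and 2.8 points at 10%.

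A simulation with three equal centres and 20,000 runs agrees. At s = 10%, type I error is 3.8% unadjusted and 4.9% adjusted, and power is 80.3% and 83.1%.

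**Step 3: secondary measures with a preoperative value.** In units of the follow-up variance, and assuming equal variances before and after surgery, the residual variance is:

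- follow-up value alone: 1
- change from baseline: 2(1 − r)
- ANCOVA: 1 − r²

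| r | Follow-up alone | Change score | ANCOVA | Cut vs follow-up alone | Cut vs change score |
|---|---|---|---|---|---|
| 0.4 | 1 | 1.20 | 0.84 | 16% | 30% |
| 0.6 | 1 | 0.80 | 0.64 | 36% | 20% |

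Against follow-up values alone, the gain is worth 1/0.84 − 1 = 19% to 1/0.64 − 1 = 56% more patients.

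**Step 4: where the baseline argument applies.** Section 3.2 lists eleven groups of secondary endpoints. Four have a preoperative value: QLQ-C30, metabolic laboratory values, malabsorption laboratory values, and impedance with handgrip. The other seven do not: Clavien grade, specific complications, length of stay, readmission, EEN tolerance, time to caloric target and resting energy expenditure. CCI has no baseline either, so Step 3 does not bear on the primary analysis.

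**The case against.** The strongest reply is that the primary test errs on the safe side and by little. That stands. Type I error falls below 5%, so a positive result would not be made less credible, and at plausible centre shares the loss is at most about 3 points of power.

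A reader might infer more than the documents support:

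- **That every analysis is an unadjusted t-test or chi-squared test.** Section 5.1 sets QLQ-C30 apart for repeated-measures tests. What remains open there is which test is meant and whether centre and the preoperative score enter it.
- **That most secondary endpoints have an unused baseline.** By endpoint group it is four of eleven, or three without QLQ-C30.
- **That adjustment would lift power from about 79% to 83%.** The 79% applies only if centre explains nothing. Where centre does matter, stratification also makes the unadjusted contrast more precise, so the fair comparison at 10% is 80.6% against 83.4%.
- **That the trial is underpowered for this reason.** The 57 and 72 per group reproduce.

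The ANCOVA gain also depends on how the t-test is applied. Section 5.1 does not say whether follow-up values or changes are compared, which is why both comparisons are shown.

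Finally, the full covariate list is commonly left to an analysis plan, and section 5.2 suggests that some adjustment is intended. But section 5.1 does not leave the method open: it names tests that have no place for a covariate. That mismatch remains.

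**Conclusion.** The point holds in a limited form. The protocol stratifies by centre and then states a primary test that ignores centre. Its t-tests and chi-squared tests for secondary endpoints use neither centre nor a baseline covariate, and the adjustment variables in section 5.2 belong to no stated analysis.

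For CCI the consequence is small and conservative: about 0.5 to 2.8 points of power for an assumed centre share of 2% to 10%. This is not a threat to the validity of the primary result.

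For laboratory values, impedance and handgrip, the loss could be larger. Its size depends on a correlation the protocol does not give and on an outcome form (follow-up value or change) it does not state. The direction of both effects is secure; the sizes rest on the assumptions shown. The change is worth making because it costs almost nothing, and it should be made before the data are analysed so that the model is not chosen in the light of the results.

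**What to change.** Amend section 5.1 and the synopsis as follows:

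- **CCI:** a linear model with arm and centre, reporting the adjusted mean difference with its 95% confidence interval.
- **Laboratory values, impedance, handgrip:** ANCOVA with arm, centre and the preoperative value, or a mixed model with the same terms where the measure is repeated.
- **QLQ-C30:** name the repeated-measures method and include centre and the preoperative score. Carry the exception into the synopsis.
- **Binary endpoints:** an analysis stratified by centre.
- **Section 5.2:** name the adjustment variables and tie them to these models, or remove the reference.

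The cost is analysis wording only. The variables are already collected, the planned software can fit these models, and the sample size stays at 144.
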